## Abstract

**Background:**

Apart from the mean level of glycemic control, the extent of glucose excursions is another important issue to consider in type 2 diabetes mellitus (T2DM) management. Studies have showed that fluctuations of glucose seem to have more deleterious effects than sustained hyperglycemia in the development of diabetic complications as acute glucose swings activate the oxidative stress. However, until now, no randomized controlled trials have been conducted with the primary aim to evaluate glycemic fluctuation in the comparison between twice-daily exenatide and other treatment paradigms (for example, biphasic insulin aspart 30).

**Methods/design:**

This multicenter, open-label, randomized, parallel trial includes a 1-week screening period and a 16-week treatment period. After the screening period, 150 patients with confirmed type 2 diabetes who are treated with stable, maximum-tolerated doses of metformin will be randomly assigned to one of two groups for antihyperglycemic therapies: exenatide and biphasic insulin aspart 30. The treatment with exenatide will be initiated at a low dose of 5 μg twice a day for 4 weeks and then titrated up to a standard dose of 10 ug twice a day until the completion of the study. The adjustment of insulin dose is instructed to achieve an optimal balance between glycemic control and the risk of hypoglycemia as dictated by clinical practice. The primary outcome is the absolute change of mean amplitude of glycemic excursion from baseline to week 16, which is calculated based on a real-time continuous glucose monitoring system (CGMS).

**Discussion:**

This is the first randomized controlled trial using a CGMS to evaluate glycemic fluctuation between twice-daily exenatide and insulin aspart 30, which will provide beneficial evidence of exenatide usage in patients with T2DM.

**Trial registration number:**

NCT02449603. Date of registration: 11 May 2015.

## Background

Due to the rapid change in the Western diet and sedentary lifestyle, China has become one of the countries with the largest number of people suffering from diabetes in the world. The most recent two nationwide diabetes surveys indicated that the prevalence of type 2 diabetes mellitus (T2DM) has reached 9.7 % and 11.6 % [1, 2], translating into 92.4 million and 113.9 million patients in China [1, 2], respectively.

Uncontrolled T2DM is associated with long-term microvascular complications, such as retinopathy, nephropathy, and neuropathy, as well as cardiovascular events that are dangerous and even fatal. Strict glucose management is thus required. In current clinical practice guidelines, the first-line medication for T2DM is metformin. When oral therapies fail to provide adequate glycemic control, the common treatment paradigm is to initiate insulin therapy [3] such as biphasic insulin aspart 30. For example, nearly 70 % of Chinese patients who are initiating insulin therapy choose premixed insulin [4]. Previous studies have shown that, in combination with metformin, twice-daily biphasic insulin aspart 30 before breakfast and dinner improves glycemic control more than metformin plus glyburide or biphasic insulin aspart 30 alone [5].

An emerging treatment option for patients failing to respond to oral antidiabetic drugs is glucagon-like peptide-1 receptor agonist (GLP-1RA) [3]. Exenatide is an incretin mimetic that shares several glucoregulatory actions with the incretin glucagon-like peptide-1, including the enhancement of glucose-dependent insulin secretion, the suppression of inappropriately elevated postprandial glucagon secretion, the reduction of food intake, and the slowing of gastric emptying [6, 7]. Placebo-controlled studies have shown that exenatide-treated T2DM patients that are suboptimally controlled with oral glucose-lowering agents can exhibit improved glycemic control, together with the additional benefit of sustained weight reduction [8–12].

Apart from the mean level of glycemic control, the extent of glucose excursions is another important issue in T2DM management. Some studies have shown that glucose fluctuations seem to have more deleterious effects than sustained hyperglycemia in the development of diabetic complications as acute glucose swings activate oxidative stress [13, 14]. Recent studies have indicated that glycemic variability might play a role in the pathogenesis of atherosclerosis and may be an independent risk factor for cardiovascular complications in diabetic patients [15]. Previous studies have also suggested that exenatide may provide a better improvement of glucose variability with similar glycemic control than insulin aspart 30 [16]. However, until now, no randomized controlled trial has been conducted with the primary aim to evaluate glycemic fluctuation in the comparison between twice-daily exenatide and other treatment paradigms (for example, biphasic insulin aspart 30).

This randomized controlled study aimed to demonstrate whether exenatide, compared to biphasic insulin aspart 30, could provide a superior improvement of glycemic excursion (assessed by continuing glucose monitor system (CGMS)) and a better improvement of inflammatory and oxidative stress markers after a 16-week treatment in Chinese T2DM patients who failed to improve on metformin monotherapy.

## Methods/design

This multicenter, open-label, randomized, parallel trial, which includes a 1-week screening period and a 16-week treatment period, is planned to start in June 2015 and complete in September 2016.

### Study population and eligibility criteria

A total of 150 subjects will be enrolled. Subjects should fulfil the following criteria:Provide informed consent prior to any study specific procedures.Men and women (nonpregnant and using a medically approved birth-control method) between 18 and 70 years of age at screening.Confirmed type 2 diabetes with history of at least half a year.Treatment with stable, maximum-tolerated doses of metformin (≥1500 mg/d, ≥ 3 months).HbA1c ≥ 7.5 % and ≤ 10.0 % at screening or within 4 weeks prior to screening (by local laboratory).Body mass index: 21 to 35 kg/m^2^.

Subjects should not enter the study if any of the exclusion criteria in Appendix 1 are fulfilled.

### Interventions

The trial will include a 1-week screening period of stable doses of metformin (1500 mg) and a 16-week treatment period. Patient will take the first dose after randomization on Day 1. The investigational products of exenatide and biphasic insulin aspart 30 will be administered through subcutaneous injection. The background product of metformin will be taken orally at 500 mg three time daily until the completion of the study.

Exenatide (AstraZeneca) should be initiated, 60 minutes before breakfast and before dinner, at a low dose of 5 ug twice a day for 4 weeks and then titrated up to a standard dose of 10 ug twice a day until the completion of the study.

Biphasic insulin aspart 30 (Novo Nordisk) will be started at a dose of 0.2 to 0.4 IU/kg, or 10 to 12 IU/d, assigned to before breakfast or before dinner in a 1:1 ratio. The adjustment of the insulin dose will be instructed to achieve an optimal balance between glycemic control and the risk of hypoglycemia as dictated by clinical practice. It will be titrated to glucose targets of fasting plasma glucose (FPG) and predinner plasma glucose < 7 mmol/L. Insulin dose titration will be based on the average self-monitored blood glucose (SMBG) results for 3 days preceding visits, unless hypoglycemia occurs. If hypoglycemia occurs, titration will be temporarily postponed, and the reasons of hypoglycemia will be evaluated. Subjects could not increase the total daily dose by more than 10 U at any time. After visit 2 (week 0), insulin doses will be titrated weekly for the first 12 weeks, then every 2 weeks thereafter according to the titration algorithm (Table 1).

**Table 1 Tab1:** Prebreakfast and predinner insulin titration regimens

Fasting and/or predinner SMBG PG value (mmol/L)	Adjustment
<5.0	-2 U
5.0 to 7.0	No adjustment
7.1 to 7.7	+2 U
7.8 to 10	+4 U
>10	+6 U

BG, blood glucose; SMGB, self-monitored blood glucose

Glycemic targets for titration: Prebreakfast and predinner PG: 5.0 to 7.0 mmol/L. Prebreakfast dose of biphasic insulin aspart 30 is titrated based on the three mean predinner PG values for the 3 days prior to the visit. Predinner dose of biphasic insulin aspart 30 is titrated based on the three mean fasting PG values for the 3 days prior to the visit. The predinner biphasic insulin aspart 30 titration is not increased if the preceding day’s bedtime SMGB value is 5.6 mmol/L

### Outcomes

The primary and secondary outcomes are shown in Table 2.

**Table 2 Tab2:** Primary and secondary outcomes

	Outcome measure:
Primary outcome	
To compare the effect of exenatide versus biphasic insulin aspart 30 on glucose variability in T2DM patients inadequately controlled with metformin monotherapy.	Absolute change of MAGE from baseline to Week 16
Secondary outcome	
To compare the effect of exenatide versus biphasic insulin aspart 30 on inflammatory and oxidative stress markers, HbA1c, weight, risk of hypoglycemia and cardiovascular risk markers.	HbA1c at baseline and Week 16
	Hours of hypoglycemia assessing by CGMS at baseline and Week 16
	SMBG at baseline and Week 16
	Blood pressure and lipids at baseline and Week 16
	Body weight, BMI and WC at baseline and Week 16
	Inflammatory markers (MCP-1, hs-CRP) at baseline and Week 16
	Urinary albumin at baseline and Week 16
Safety outcome	
To evaluate the safety and tolerability of exenatide in relation to biphasic insulin aspart 30.	Adverse events/serious adverse events
	Vital signs
	Clinical hypoglycemia
	Collection of clinical chemistry/hematology parameters
	Electrocardiogram

T2DM, type 2 diabetes mellitus; MAGE, mean amplitude of glycemic excursion; CGMS, continuous glucose monitoring system; BMI, body mass index; WC, waist circumference; MCP-1, monocyte chemotactic protein-1; hs-CRP, high-sensitivity C-reactive protein

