Blood glucose (BG) is monitored in the study sites by a Guardian™ Real-Time CGMS (Medtronic MiniMed Inc., CA, USA), which is used to record glucose levels every 5 min for 72 h consecutively. During the second visit (baseline visit) and the last visit (end of the study), the continuous glucose sensor is inserted subcutaneously in the abdominal periumbilical area, separately. Meanwhile, a blood glucose meter is used to perform sensor calibration four times daily. The participants receive a calibration 2 hours after sensor insertion and then four glucose calibrations at each meal and before bed, and the time of each meal is marked in the consecutive 3-day test. Participants are provided the same mixed meals (30 kcal/kg ideal weight/day, based on dietitian recommendations, including 55 % of calories from carbohydrates, 25 % from fat and 20 % from proteins, with a meal distribution of 1/5, 2/5 and 2/5). They must keep a diary of meals (content and times) and avoid intensive physical activity during both CGMS periods. The dietary pattern using 3-day diet records for each CGMS study period will be checked in all participants. All the parameters of continuous glucose monitoring are calculated from each CGMS output, which is extracted using the CGMS 3.0 software package (Medtronic MiniMed, MMT-7310 version 3.0C (3.0.128), CA, USA). The mean glucose level is calculated as the mean of all the consecutive sensor readings, from which the SD is also calculated. The largest amplitude of glycemic excursion (LAGE) is defined as the maximal sensor glucose level minus the minimal sensor glucose level during each day. The MAGE is used for assessing the intraday glucose variability. MAGE is calculated by measuring the arithmetic mean of the differences in consecutive peaks and nadirs, which are taken into consideration only if they exceed one standard of deviation from the mean [18]. The mean of the daily differences (MODD), calculated as the average absolute difference of paired sensor glucose values during two successive 24-h periods, is used to assess the interday glucose variability.

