### Statistical methods

The primary analysis population will be based on the full analysis set (FAS) and will include all randomized patients, according to the intention-to-treat (ITT) basis. All supportive analyses will be based on per-protocol set (PPS) analysis set, and the safety endpoints will be analyzed on safety analysis set (SS). The research has no plans to implement interim analysis.

All data will be entered into SPSS 10.0 software (SPSS Inc., Chicago, IL). Analyses by actual therapy include only those patients who are continuing to take their allocated therapy. Data are presented as mean and SD, range, or percentage. Data will be examined for skewness, outliers, and systematic missing data. Transformations will be undertaken as needed. Univariate and multivariate tests for repeated measures (ANOVA) are used to evaluate differences within and between groups over time. Mann–Whitney *U* test is used to evaluate differences between groups, whereas Friedman’s test (variance analysis) followed by Wilcoxon paired test is used to evaluate differences within groups. *P* < 0.05 is considered significant.

All efficacy endpoints will be analyzed in FAS, using a covariance model. Point estimates and SD for the mean change within each treatment group will be estimated. Difference within and between groups over time will be analyzed using covariance test. A last observation carried forward (LOCF) analysis will be presented for each efficacy assessment as sensitivity analysis unless otherwise specified.

The safety endpoints will be analyzed on SS. Adverse events will be summarized. The incidence of adverse events will be summarized by body system organ class and preferred term. Analyses for safety and tolerability endpoints will be summarized using descriptive statistics for continuous variables or frequency counts and percentages for categorical variables.

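### The risk-of-hypoglycemia objective is tied to one 72-hour on-treatment CGMS recording, while 16-week clinical hypoglycemia is tabulated without a between-arm estimate

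*Protocol article*

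**What the plan says.** All references are to the protocol article.

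- **Objective.** Table 2 (Outcomes) has a secondary objective to compare exenatide with biphasic insulin aspart 30 on a list that includes "HbA1c, weight, risk of hypoglycemia and cardiovascular risk markers".
- **Measure for it.** The one hypoglycemia measure in the secondary block is "Hours of hypoglycemia assessing by CGMS at baseline and Week 16". SMBG is listed there too, but no hypoglycemia measure is defined from it.
- **The recording.** Data collection and management describes a device "which is used to record glucose levels every 5 min for 72 h consecutively". On timing it says: "During the second visit (baseline visit) and the last visit (end of the study), the continuous glucose sensor is inserted subcutaneously". Table 3 agrees, with CGMS at V2 and V9 only.
- **Insulin titration.** Under Interventions, "insulin doses will be titrated weekly for the first 12 weeks, then every 2 weeks thereafter".
- **Clinical hypoglycemia.** Table 2 lists it as a safety outcome. Table 3 has no separate row for it, but adverse events are recorded at every visit from V2 to V9, and Data collection and management says they are collected throughout the study.
- **Analysis.** Statistical methods assigns efficacy endpoints a covariance model in the full analysis set, with LOCF as sensitivity analysis. For safety: "Analyses for safety and tolerability endpoints will be summarized using descriptive statistics for continuous variables or frequency counts and percentages for categorical variables".

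**The concern.** The objective is comparative and concerns risk over treatment. The measure assigned to it is a three-day snapshot at the end. The data that span treatment sit in another block of Table 2, under an analysis rule that produces no estimate of the difference between arms.

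The timing matters because insulin doses respond to glucose readings. Titration is postponed when hypoglycemia occurs, and Table 1 includes a downward step. By week 16 the insulin dose has already been shaped by earlier low readings, and that earlier experience is what the recording cannot show.

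Follow-up matters because a crude percentage of patients with an event treats someone who left at week 3 like someone followed to week 16. If dropout differs in timing or frequency between arms, the percentages are not comparable.

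At stake is the hypoglycemia conclusion. The Discussion cites a lower hypoglycemia risk with exenatide in earlier work, so readers will look for this result. As written, a null result on three days of CGMS could be presented as the formal answer.

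**Working it through.** **The plan's own figure.** The article gives no event rate, power or sample size for hypoglycemia. Its only power statement is for MAGE: 75 per group, 15 % dropout, SD 3.0 and difference 1.6 mmol/L, at least 85 %.
- Evaluable per arm: 75 × 0.85 = 63.75.
- Standardized difference: 1.6 / (3.0 × √(2/63.75)) = 3.01.
- Power: Φ(3.01 − 1.96) = 0.853.

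This reproduces, and the present point does not touch it.

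**Share of treatment time behind the CGMS measure.**
- Treatment period: 16 × 7 × 24 = 2,688 h.
- On-treatment recording: 72 h. The other recording is at the randomization visit. Since randomization is stratified on MAGE, that recording has to precede treatment.
- Share: 72 / 2,688 = 2.7 %.
- With the ±7-day window on the last visit: 72 / (119 × 24) = 2.5 % to 72 / (105 × 24) = 2.9 %.
- Full-period data cover 2,688 / 72 ≈ 37 times as much time per completer.

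This counts the last recording as wholly on treatment. The sensor is inserted at the final visit, so that is the favourable assumption.

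**Position relative to titration.** The earliest permitted last visit is day 112 − 7 = 105, the end of week 15. No part of the recording can fall in weeks 0 to 12, the weekly phase. It can fall within or after the two-weekly phase.

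**Unequal follow-up.** At 15 % dropout, 0.15 × 150 = 22.5 patients leave early. Someone who leaves without a week-16 recording has only the baseline CGMS value, and LOCF would carry that pre-treatment value forward.

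**What the full-period data could support.** The rates here are assumptions: 1 to 6 clinical episodes per patient-year on aspart 30, half that on exenatide, 63.75 per arm followed for 112 days.
- Mean episodes per patient: μ = rate × 112/365. At 4 per year, μ₁ = 1.23 and μ₂ = 0.61, so about 78 against 39 episodes.
- Variance of the log rate ratio with dispersion k: [(1/μ₁ + k) + (1/μ₂ + k)] / 63.75.
- Power at 4 per year, two-sided 0.05: 94 % (k = 0), 75 % (k = 1), 59 % (k = 2).
- Over 1 to 6 per year: from 32 % (rate 1, k = 2) to 99 % (rate 6, k = 0). At k = 2 alone, 32 % to 65 %.

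The full-period comparison can therefore be informative, but it is not guaranteed to be decisive. Hence the emphasis on an estimate with an interval.

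**The case against.** **Hypoglycemia would still be seen over 16 weeks.** Clinical hypoglycemia is a named safety outcome, the safety objective is itself worded relative to aspart 30, and counts by arm would be shown. This stands. A reader might infer that hypoglycemia is compared on only about 3 % of exposure, and the documents do not support that. What is absent is a planned estimate and interval for the full period.

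**Descriptive safety reporting is common in a study that calls itself a pilot, and modelling detail belongs in an SAP.** This stands in part. The choice of regression could be left to an SAP. But the article itself states which measure serves the objective and that safety endpoints are described, so this is a choice made in the text.

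**A sensor is objective in an open-label trial.** This stands. Clinical episodes may be found more often in the arm that self-monitors more, and insulin titration depends on SMBG. It is a good reason not to displace CGMS hours.

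**Other stronger readings that do not hold.**
- That the recording misses all titration: two-weekly adjustment continues after week 12, and the algorithm includes no change and a decrease.
- That the conditions of the recording lower hypoglycemia: "Participants are provided the same mixed meals" and they must "avoid intensive physical activity during both CGMS periods", but habitual diet is not given and nothing in the article supports a direction for the meals.
- That the CGMS comparison has almost no power: a calculation on clinical episodes within 72 h concerns an endpoint nobody plans to test. The planned endpoint is hours, from readings every 5 minutes, and the article gives no variance for it.
- That patients who stop early contribute nothing: the full analysis set includes all randomized patients, and the article does not say that early stoppers forgo the final recording.

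**Conclusion.** The point holds as a mismatch between a stated objective and its stated measure and analysis. The comparative hypoglycemia objective has one listed measure, whose on-treatment data cover 2.7 % of the 16 weeks (2.5 % to 2.9 % across the visit window) and none of weeks 0 to 12. The full-period clinical data receive counts and percentages, with no between-arm estimate and no adjustment for follow-up time.

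These statements rest on the article's own figures and need no assumed event rate. One inference is involved: that clinical hypoglycemia is captured across the whole period follows from the adverse-event schedule, since it has no row of its own in Table 3.

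The consequence is limited to a secondary objective. The primary endpoint, its power and the sample size stand.

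**What to change.** 1. **Table 2.** Keep week-16 CGMS hours under the risk-of-hypoglycemia objective as the objective measure. Add clinical hypoglycemia from week 0 to week 16 alongside it.
2. **Statistical methods.** For clinical hypoglycemia, in all treated patients including those who stop early, give:
   - the rate ratio between arms with 95 % CI, from negative binomial regression with log follow-up time as offset;
   - the difference between arms in the proportion with at least one episode, with 95 % CI.
3. **Reporting.** Present the CGMS and clinical results together, so that neither is read alone as the answer to the objective.

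The cost is a wording change in two places, one extra model and one difference in proportions, on data already collected. No visit, dose or clinical rule changes. The downside is that open-label clinical episodes may be ascertained unequally. The CGMS hours are retained for that reason, and the caveat should be stated with the result.

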### Participant timeline

The time schedule for the enrollment, interventions, assessments, and visits for participants are shown in Table 3.

**Table 3 Tab3:** Study plan detailing the procedures

Study Period	Screening	Treatment							
Visit	V1	V2	V3	V4	V5	V6	V7	V8	V9
		Randomization							
Week	−1	0 (baseline)	1	2	4	8	10	12	16
Day		0	±2	±2	±7	±7	±2	±7	±7
Telephone visit			×	×			×		
Screening/baseline									
Written informed consent	×								
Inclusion/exclusion criteria	×	×							
Demographics	×								
Physical examination	×	×			×	×		×	×
Medical/current conditions	×	×	×	×	×	×	×	×	×
History of diabetes & complications	×								
Lifestyle instruction	×	×	×	×	×	×	×	×	×
Treatment									
Drug dispensing and accountability		×			×	×		×	
Concomitant medications	×	×	×	×	×	×	×	×	×
SMBG			×	×	×	×	×	×	×
Insulin titration			×	×	×	×	×	×	
Safety assessments									
Pregnancy test (urine)	×								×
Physical examination	×	×			×	×		×	×
Vital signs	×	×			×	×		×	×
12-lead ECG	×								×
Hematology panel	×								×
Urinalysis	×								×
Liver function	×								×
Creatinine, BUN, uric acid	×								×
Lipids	×				×				×
Adverse events		×	×	×	×	×	×	×	×
Efficacy assessments									
HbA1c	×								×
Fasting plasma glucose	×	×			×	×		×	×
Fasting insulin and C-peptide		×							×
CGMS		×							×
Standard meal test:2 h PPG, insulin and C-peptide		×							×
BW, BMI and WC	×	×			×	×		×	×
Other assessment									
MCP-1, hs-CRP		×							×
8-Iso-PGF2α		×							×
Urinary albumin		×							×

SMBG, self-monitoring of blood glucose; ECG, electrocardiogram; BUN, blood urea nitrogen; CGMS, continuous glucose monitoring system; PPG, postprandial plasma glucose; BW, body weight; BMI, body mass index; WC, waist circumference; MCP-1, monocyte chemotactic protein-1; hs-CPR, high-sensitivity C-reactive protein; 8-Iso-PGF2α, 8-Iso-prostaglandin F2α

